## 7. Research methods

### 7.1 Study design

This study is a prospective, open-label, randomized controlled, blinded endpoint (PROBE) trial. This trial will include adult patients with IgA nephropathy who are at high risk of renal progression.

During a 12-week run-in period, all participants will be treated with comprehensive supportive care, including blockade of RAS using losartan to reduce blood pressure to a target below 130/80 mmHg. In participants whose urinary protein excretion rate remained above 0.75g per day despite blood pressure control, the dose of losartan will be increased to the tolerable maximum daily dose as described previously. Participants will be advised for lifestyle modification to quit smoking, restrict high-salt intake, and avoid nephrotoxic drugs. Anemic patients with a hemoglobin level lower than 110g/L were treated with erythropoietin. Statin was used when necessary. Dietary sodium intake

were monitored by urinary sodium excretion rate (or chloride excretion rate in patients treated with sodium bicarbonate) measured by 24-hour urine sample.

By the end of run-in period, participants who have persistent proteinuria, defined as urinary protein excretion rate above 0.75g and lower than 3.5g per day, eGFR over 30 ml/min/1.73m^2, and those who are willing to participate the study entered the 3-year trial phase and will be randomly assigned to MMF plus supportive care or to supportive care alone. Participants who are not tolerable to losartan (eGFR decline over 30% of baseline or developing hyperkalemia) during run-in phase will not undergo randomization.

Participants will be randomly assigned to the MMF plus supportive care group received oral administrated MMF at a daily dose of 1.5g for 12 months and then tapered to a maintained daily dose of 0.75g to 1.0g for at least 6 months. Both MMF plus supportive care and supportive care alone group stayed on supportive care as in run-in period. Participants will continue to be followed at regular intervals for a planned 3 years.

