#### **7.9 Visits**

Information to be collected at the visits are summarized in Table 1.

269 **Table 1: Tabulated overview on data collected during the study**

| Phase                              | Screening | Run-in |    |    |   | Treatment period |   |    |    |    |    |    |    |    |    |    |    |    |    |    |     |     |     |     |     |     |     |     |  |
|------------------------------------|-----------|--------|----|----|---|------------------|---|----|----|----|----|----|----|----|----|----|----|----|----|----|-----|-----|-----|-----|-----|-----|-----|-----|--|
| Visits                             | 1         | 2      | 3  | 4  | 5 | 6                | 7 | 8  | 9  | 10 | 11 | 12 | 13 | 14 | 15 | 16 | 17 | 18 | 19 | 20 | 21  | 22  | 23  | 24  | 25  | 26  | 27  | 28  |  |
| Time (week)                        | -14       | -12    | -8 | -4 | 0 | 4                | 8 | 12 | 16 | 20 | 28 | 36 | 44 | 52 | 60 | 68 | 76 | 78 | 86 | 94 | 102 | 110 | 118 | 126 | 134 | 142 | 150 | 156 |  |
| Informed consent form              |           | x      |    |    |   |                  |   |    |    |    |    |    |    |    |    |    |    |    |    |    |     |     |     |     |     |     |     |     |  |
| In/exclusion criteria              |           | x      |    |    |   |                  |   |    |    |    |    |    |    |    |    |    |    |    |    |    |     |     |     |     |     |     |     |     |  |
| Medical history/
demography     | x         |        |    |    |   |                  |   |    |    |    |    |    |    |    |    |    |    |    |    |    |     |     |     |     |     |     |     |     |  |
| Height, weight                     | x         | x      | x  | x  | x | x                | x | x  | x  | x  | x  | x  | x  | x  | x  | x  | x  | x  | x  | x  | x   | x   | x   | x   | x   | x   | x   | x   |  |
| Physical examination               | x         | x      |    |    | x |                  |   |    |    |    |    |    |    |    |    |    |    |    |    |    |     |     |     |     |     |     |     | x   |  |
| Vital signs                        | x         | x      | x  | x  | x | x                | x | x  | x  | x  | x  | x  | x  | x  | x  | x  | x  | x  | x  | x  | x   | x   | x   | x   | x   | x   | x   | x   |  |

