**Treatment period**

**Visit 6-18**

Patients who are assigned to the MMF group will received oral administrated MMF at a daily dose of 1.5g for 12 months and then tapered to a maintained daily dose of 0.75g to 1.0g for at least 6 months. Patients who are assigned to the supportive care group will stay on supportive care as in run-in period. Participants will receive routine follow-up every 4 weeks in the first 6 months and then every 8 weeks.

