**Visit 19-28**

During follow-up, participants will continue to receive routine follow-up every 8 weeks.

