## 3.6. Secondary Outcomes

There are four secondary outcomes.

- 1) The time to 30% reduction in eGFR from the baseline.
- 2) Annual absolute changes in the eGFR (eGFR slope) over the trial period.
- 3) Rapid eGFR decline ( $< -5 \text{ ml/min/1.73m}^2/\text{year}$ ).
- 4) Percentage change in the rate of urinary protein excretion at the end of trial over the baseline.

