| Screening log                      | ×         |        |    |    |   |                  |   |    |    |    |    |    |    |    |    |    |    |    |    |    |     |     |     |     |     |     |     |     |   |  |  |  |  |
| Randomization                      |           |        |    |    | × |                  |   |    |    |    |    |    |    |    |    |    |    |    |    |    |     |     |     |     |     |     |     |     |   |  |  |  |  |
| Blood chemistry        | ×         |        | ×  |    | × | ×                | × | ×  | ×  | ×  | ×  | ×  | ×  | ×  | ×  | ×  | ×  | ×  | ×  | ×  | ×   | ×   | ×   | ×   | ×   | ×   | ×   | ×   | × |  |  |  |  |
| Hematology                         | ×         |        | ×  |    | × | ×                | × | ×  | ×  | ×  | ×  | ×  | ×  | ×  | ×  | ×  | ×  | ×  | ×  | ×  | ×   | ×   | ×   | ×   | ×   | ×   | ×   | ×   | × |  |  |  |  |
| Urinary analysis                   | ×         |        | ×  |    | × | ×                | × | ×  | ×  | ×  | ×  | ×  | ×  | ×  | ×  | ×  | ×  | ×  | ×  | ×  | ×   | ×   | ×   | ×   | ×   | ×   | ×   | ×   | × |  |  |  |  |
| 24-hour urine protein  | ×         |        | ×  |    | × | ×                | × | ×  | ×  | ×  | ×  | ×  | ×  | ×  | ×  | ×  | ×  | ×  | ×  | ×  | ×   | ×   | ×   | ×   | ×   | ×   | ×   | ×   | × |  |  |  |  |
| Diet education                     | ×         | ×      | ×  | ×  | × | ×                | × | ×  | ×  | ×  | ×  | ×  | ×  | ×  | ×  | ×  | ×  | ×  | ×  | ×  | ×   | ×   | ×   | ×   | ×   | ×   | ×   | ×   | × |  |  |  |  |
| Study drug dispensation            |           |        |    |    |   | ×                | × | ×  | ×  | ×  | ×  | ×  | ×  | ×  | ×  | ×  | ×  | ×  |    |    |     |     |     |     |     |     |     |     |   |  |  |  |  |
| Concomitant medications            | ×         | ×      | ×  | ×  | × | ×                | × | ×  | ×  | ×  | ×  | ×  | ×  | ×  | ×  | ×  | ×  | ×  | ×  | ×  | ×   | ×   | ×   | ×   | ×   | ×   | ×   | ×   | × |  |  |  |  |
| AEs/SAEs                           |           |        | ×  | ×  | × | ×                | × | ×  | ×  | ×  | ×  | ×  | ×  | ×  | ×  | ×  | ×  | ×  | ×  | ×  | ×   | ×   | ×   | ×   | ×   | ×   | ×   | ×   | × |  |  |  |  |
| Endpoints                          |           |        |    |    |   | ×                | × | ×  | ×  | ×  | ×  | ×  | ×  | ×  | ×  | ×  | ×  | ×  | ×  | ×  | ×   | ×   | ×   | ×   | ×   | ×   | ×   | ×   | × |  |  |  |  |

215

216

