#### **6.3.3.4. Percentage Changes in the Rate of Urinary Protein Excretion Rate**

The baseline 24-hour UPE is calculated as the mean of the two 24-hour UPE value from Visit 4 (pre-randomization visit) and Visit 5 (randomization visit). The 24-hour UPE at exit is calculated as the mean of from the last two visits before study exit. Percentage change is calculated as 100% x (exit value-baseline)/baseline. The difference in the percentage change between the two treatment groups will be tested using unpaired two-sample t-test.

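### The only prespecified efficacy test of proteinuria is read at an undefined study exit, for completers more than 15 months after the last scheduled MMF dispensing, so it does not estimate the effect during treatment

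*Combined protocol and SAP*

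**What the plan says.** **The outcome.** SAP 3.6 lists the fourth secondary outcome as "Percentage change in the rate of urinary protein excretion at the end of trial over the baseline". The efficacy list in the protocol abstract uses the same timing; protocol 7.7 gives none.

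**The test.** SAP 6.3.3.4 defines the follow-up value: "The 24-hour UPE at exit is calculated as the mean of from the last two visits before study exit". It then states: "The difference in the percentage change between the two treatment groups will be tested using unpaired two-sample t-test". Neither document defines study exit or ties it to a week.

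**The treatment course.** Protocol 7.9 (Visits 6-18) gives MMF as a "daily dose of 1.5g for 12 months and then tapered to a maintained daily dose of 0.75g to 1.0g for at least 6 months". Protocol 7.1 adds: "Participants will continue to be followed at regular intervals for a planned 3 years". In Table 1 of both documents, the row "Study drug dispensation" is marked at Visits 6 to 18 (weeks 4 to 78) and at no later visit. For Visits 19-28 the protocol says only: "During follow-up, participants will continue to receive routine follow-up every 8 weeks". The week row of Table 1 ends "134 | 142 | 150 | 156". Table 1 schedules 24-hour urine protein at every visit from Visit 5, including weeks 76 and 78.

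**Related rules.** SAP 4.3 allows no imputation for primary and secondary endpoints. SAP 5.1 puts all efficacy analyses on everyone randomized. SAP 6.2 plots urine protein excretion (UPE) by visit, with missing values filled by LOCF and no test. SAP 3.7.2 lists 24-hour UPE among the laboratory examinations. SAP 6.4.2 fits laboratory variables with a treatment-by-time mixed model, within the safety analysis on the safety set.

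**The concern.** Two things do not fit together.

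First, the tested value is taken long after scheduled dispensing ends. The test therefore says whether a proteinuria difference is still present near year 3. It does not say whether MMF lowered proteinuria while it was being given. If the exit result is null, the reader cannot tell a drug with no antiproteinuric effect from one whose effect waned after it was stopped. The urine samples that could separate these are already scheduled, but no efficacy test uses them.

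Second, study exit is a different week for each early leaver. A patient who leaves at week 12 contributes weeks 8 and 12. If the outcome is meant to be an end-of-trial value, that is in effect a last observation carried forward, which sits badly with SAP 3.6 and with the no-imputation rule in SAP 4.3.

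**Working it through.** **1. The plan's own course length.** One month = 365.25 / 12 / 7 = 4.348 weeks. The minimum course is 12 + 6 = 18 months, and 18 × 4.348 = 78.3 weeks. This agrees with the last dispensing mark in Table 1 (Visit 18, week 78), half-way through the 156 weeks.

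**2. Gap for a completer, from the last scheduled dispensing visit.**
- If the last two visits are Visits 27 and 28: (150 + 156) / 2 = week 153; 153 − 78 = 75 weeks; 75 / 4.348 = 17.2 months.
- If Visit 28 is itself the exit and the two visits before it are meant: (142 + 150) / 2 = week 146; 146 − 78 = 68 weeks; 68 / 4.348 = 15.6 months.

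The text allows both readings.

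**3. Time off drug may be shorter.** If the week-78 supply lasts 8 weeks, to week 86 (an assumption), the two gaps become 67 weeks (15.4 months) and 60 weeks (13.8 months). Maintenance is a minimum with no stated maximum, so individual patients could be off drug for less time still.

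**4. How many leave before week 78.** Protocol 7.4 plans for 10% loss over 3 years and 84 per group. With a constant hazard (an assumption), the share lost by week 78 is 1 − (1 − 0.10)^0.5 = 5.1%, and 0.051 × 84 = 4.3 patients per arm. If the 3-year loss were 5% or 20%, the share would be 2.5% or 10.6%.

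If primary events also ended follow-up, which the documents do not state, the planning rates of 16% and 36% would give:
- MMF: 1 − (0.84 × 0.90)^0.5 = 13%
- Control: 1 − (0.64 × 0.90)^0.5 = 24%

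**5. What the exit contrast keeps of the on-drug contrast.** Let s be the share of MMF patients whose exit value is on drug, and f the fraction of the effect that persists off drug. The ratio is about s + (1 − s)f. Here every early leaver is taken to be on drug and every completer off drug.

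| Persistence f | s = 0.05 | s = 0.13 |
|---|---|---|
| 0 | 0.05 | 0.13 |
| 0.5 | 0.53 | 0.57 |
| 1 | 1.00 | 1.00 |

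The documents give no value for f. The table shows that f, not s, decides the answer.

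**6. Whether another analysis fills the gap.** SAP 6.2 is descriptive and uses LOCF. SAP 6.4.2 would give a contrast at each visit, but it names urine analysis and not UPE, which SAP 3.7.2 lists as a separate item. The safety set in SAP 5.2 leaves out participants who took no study medication. Read literally, that may remove the supportive-care arm. Whether this model covers UPE, or has controls in it, cannot be settled from the text.

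**The case against.** The strongest reply is that the exit comparison is what the plan set out to measure. The strategy under test is a limited MMF course with 3 years of follow-up, analysed in all randomized patients, and the outcome is stated for the end of the trial. Comparing the arms near year 3 is a legitimate treatment-policy question about durable benefit. This stands. A reader might infer that the outcome cannot show what MMF does to proteinuria. The documents do not support that, because the exit contrast reflects the on-drug effect to the extent that the effect lasts.

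Three further points also stand, in whole or in part:

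- **Early leavers.** It is tempting to say that dropout turns the MMF arm into a serious mixture of on-drug and off-drug values. At the planned loss this concerns about 4 of 84 patients per arm. Some of them may already have stopped MMF, and protocol 7.10 encourages patients who stop drug to keep attending.
- **Other analyses.** It would be too strong to say that no by-visit treatment comparison of UPE exists, because SAP 3.7.2 and 6.4.2 together may supply one. It would still be a safety-section analysis of uncertain scope.
- **Power.** A specific power for the exit test cannot be derived. It would need an on-drug effect, a standard deviation and a rate of waning, none of which the documents give.

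The reply does not remove the undefined exit, nor the absence of an efficacy contrast for the treatment period.

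**Conclusion.** The point holds as a limited one. The only prespecified efficacy test of proteinuria is read, in completers, 15.6 to 17.2 months after the last scheduled MMF dispensing, and at no fixed week in anyone else. It validly tests durable effect near year 3 but does not estimate the effect during treatment. It would retain between about 5% and 100% of an on-drug difference, depending on a persistence that the documents do not give.

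The gap rests on Table 1. Actual time off drug may be shorter because maintenance is a minimum. The 5% early-leaver share rests on the planned 10% loss and a constant hazard. The outcome is secondary and has no multiplicity control, and neither primary outcome is affected. This is an inexpensive improvement in what the trial can conclude, not a flaw that invalidates the analysis.

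**What to change.** In SAP 6.3.3.4:

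1. Keep the end-of-trial contrast, but define it as the mean of Visits 27 and 28 (weeks 150 and 156) in place of the last two visits before study exit. This agrees with SAP 3.6 and the protocol abstract.
2. Add a prespecified end-of-treatment contrast as the mean of Visits 17 and 18 (weeks 76 and 78).
3. Estimate both in the ITT set from one repeated-measures model of UPE with a treatment-by-visit interaction, in place of the t-test. Early leavers then contribute their observed visits, and their last values are not carried into either window. State the scale on which UPE is modelled, since the outcome is worded as a percentage change.

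The first contrast then addresses persistence, and the second addresses the effect at the end of the scheduled dispensing period.

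**Cost.** No visit, sample or treatment changes, because 24-hour urine protein is already scheduled at all four visits. There is one more secondary comparison without multiplicity adjustment and a little more analysis work. The model also assumes that leavers' unobserved values can be predicted from their observed ones.

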### **6.4. Safety Analysis**

The analysis of safety endpoints will be performed on the SS. For safety analysis, no formal hypothesis testing will be performed. Descriptive analysis will be performed to summarize safety events. Serious adverse events and adverse events will be summarized as the number of events and the number (%) of patients experiencing at least one event. Differences in the proportions of patients experiencing at least one event will be tested using Fisher's exact test.

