### **4.4. Multiplicity Adjustment**

For the primary analysis, a two-sided p value of <0.025 was regarded as statistically significant. For the secondary and safety analyses, no multi-test adjustment was employed, and a two-sided p value of <0.05 was regarded as statistically significant. The outcomes are clearly categorized by degree of importance (primary, secondary) and a limited number of subgroup analyses are pre-specified.

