#### 6.4.2. Laboratory Examination

Lab examination includes blood hematology, blood biochemistry, urine analysis during the screening visit. Descriptive analysis will be performed to summarize the results and clinical significance judgment of lab examination. For blood hematology, blood biochemistry, urine analysis, listings of patients with clinical significance results will be provided. The listings will be presented according to the subject ID, sex, age, date of test, examination index, examination result and/or clinical evaluation.

All measures will be summarized by use of standard measures of central tendency and dispersion using mean and standard deviation as well as quartile points at 0.25, 0.5 and 0.75 where appropriate stratified by measurement time points and by treatment group. Longitudinal mean plots will be used to display means and 95% confidence bands over time by randomized group. To assess the treatment effect on laboratory variables, a linear mixed effects model with a random intercept by subject and with treatment, time (categorical) and a treatment by time interaction as fixed effects will be used. The effect of the treatment will be assessed as the adjusted mean difference and its 95% confidence interval.

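### SAP 6.4 rules out hypothesis testing for safety and then orders Fisher's exact test, SAP 4.4 gives that test a 0.05 verdict, and no confidence interval is planned for any clinical adverse event

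*Combined protocol and SAP*

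**What the plan says.** Three statements in the SAP bear on the same between-arm comparison of adverse events.

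- SAP 6.4 opens with "For safety analysis, no formal hypothesis testing will be performed" and adds "Descriptive analysis will be performed to summarize safety events".
- The last sentence of that paragraph reads: "Differences in the proportions of patients experiencing at least one event will be tested using Fisher's exact test". It gives no significance level and no rule for reading the result.
- SAP 4.4 covers safety by name: "For the secondary and safety analyses, no multi-test adjustment was employed, and a two-sided p value of <0.05 was regarded as statistically significant".

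For what is reported, SAP 6.4 asks for the number of events and the number and percentage of patients with at least one. SAP 6.4.1 asks for number, frequency and incidence of the listed categories. Neither asks for a risk difference, risk ratio or confidence interval. Laboratory data are treated differently. SAP 6.4.2 says "To assess the treatment effect on laboratory variables, a linear mixed effects model" will be used, and expresses the effect as an adjusted mean difference with a 95% confidence interval.

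**The concern.** If the p-values were purely descriptive, SAP 4.4 would not give them a significance threshold. If they were meant as tests, SAP 6.4 would not open by ruling tests out. After the data are seen, an author could cite one sentence to call an excess statistically significant and another to say that safety was never formally tested. The SAP gives no basis for objecting to either.

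This matters because SAP 1.1 describes MMF as a potent immunosuppressive agent, the trial adds it to supportive care, and SAP 6.4.1 singles out sepsis, repeated infections, low white-cell counts and malignancy. Some of these may be infrequent in a trial of this size. For infrequent events a 0.05 verdict from Fisher's test says little, and the quantity a reader needs, the risk difference with its uncertainty, is not planned.

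**Working it through.** **Step 1. The sentences side by side.** SAP 6.4, first sentence: no formal test. SAP 6.4, last sentence: a named test. SAP 4.4: a threshold and a label for safety results. The last two fit together, one supplying the test and the other its cut-off. The first contradicts both. Neither document calls the safety p-values nominal or exploratory, or gives an order of precedence.

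**Step 2. Arm size.** Protocol 7.4 gives 76 per group before dropout and 84 after, from 36% versus 16%, 80% power and two-sided 0.05. Check with the pooled two-proportion formula, mean rate 0.26:

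n = [1.96·√(2·0.26·0.74) + 0.842·√(0.36·0.64 + 0.16·0.84)]² / 0.20² = (1.216 + 0.508)² / 0.04 ≈ 74.3, so 75 per group.

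The stated 76 is reproduced to within one patient, and 76 × 1.10 = 83.6 gives 84. I use 84 per arm below, which assumes that every randomised patient in both arms has safety data.

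**Step 3. Where the verdict changes.** If all k events fall in one arm of 84, the two-sided Fisher p-value is 2·C(84,k)/C(168,k).

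- k = 5: p = 0.059
- k = 6: p = 0.028

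So a category with five or fewer affected patients in total can never reach p<0.05, however they are split. The label also turns on one patient at higher counts: 7 versus 1 gives p=0.064 and 8 versus 1 gives p=0.034; 9 versus 2 gives p=0.057 and 10 versus 2 gives p=0.032.

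**Step 4. Power.** Power is the sum, over all pairs of counts (a, b) with Fisher p<0.05, of Bin(a; 84, p₁)·Bin(b; 84, p₂). The documents give no adverse-event rates, so these are assumptions:

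- 2% versus 8%: 28%
- 3% versus 10%: 33%
- 5% versus 15%: 51%

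With equal rates in both arms, the same sum gives an actual type I error of 0.3% at a 2% event rate, 1.7% at 5% and 2.9% at 10%. For rare events the nominal 0.05 rule is therefore far stricter than it looks.

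**Step 5. What an interval would show.** Newcombe 95% interval for 5/84 versus 0/84, in percentage points. The Wilson limits are 2.57 to 13.19 and 0 to 4.37, and the difference is 5.95.

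- Lower: 5.95 − √[(5.95 − 2.57)² + (4.37 − 0)²] = 5.95 − 5.53 = 0.4
- Upper: 5.95 + (13.19 − 5.95) = 13.2

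For 6/84 versus 0/84 the Wilson limits are 3.31 to 14.72 and 0 to 4.37, and the difference is 7.14. The lower limit is 7.14 − √[(7.14 − 3.31)² + 4.37²] = 1.3 and the upper is 14.7. The two results carry nearly the same information, 0.4 to 13.2 against 1.3 to 14.7 points, yet the 0.05 rule puts them on opposite sides of the line.

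**The case against.** The strongest defence is that the sentence ordering Fisher's test and the 4.4 threshold agree, so only the opening sentence of 6.4 is out of place, and deleting it would end the contradiction. That is correct about the wording. It would leave clinical adverse events with a low-powered verdict and no interval, while laboratory variables keep theirs.

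A second defence is that no trial of this size is powered for safety, and that the contrast between Fisher's test and an interval depends partly on method. Both points stand. For 5 versus 0 the Newcombe interval starts at 0.4 points, but an Agresti-Caffo interval runs from about −0.03 to 11.7. The case for intervals is that they show how large a harm remains compatible with the data; whether zero is excluded should not become a new pass/fail rule.

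Three stronger readings are tempting, and the documents do not support them.

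- A reader might infer that the size of any harm goes unreported. SAP 6.4 and 6.4.1 require counts, percentages and incidence, so a crude risk difference can be found by subtraction. Only the planned estimate and its uncertainty are missing.
- A reader might infer that the p-value is the only comparative safety result. SAP 6.4.2 plans between-arm laboratory differences with confidence intervals, and the panel includes white cells and transaminases.
- A reader might count every event listed in SAP 6.4.1 as a separate test and quote a family-wise false-positive rate. That section says only that the categories are summarised, so the number of tests is not fixed. Overlapping events are also not independent.

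Nor does any text say that a non-significant harm would be dismissed; that is a risk in reporting.

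**Conclusion.** The conflict between SAP 6.4 and SAP 4.4 is real. Reading the Fisher p-values as merely descriptive fails because 4.4 attaches a significance label to safety by name. The second defect is the absence of any effect estimate with a confidence interval for clinical adverse events. At 84 evaluable patients per arm, power is roughly 28% to 51% for the assumed contrasts, and one patient moves the result from p=0.059 to p=0.028. The textual conflict needs no assumptions. The power figures rest on the assumed rates and on full safety data in both arms.

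That last assumption is itself uncertain. Protocol section 9 (Collection) does not require adverse events to be documented while a patient has not used MMF. SAP 3.7.1 defines the analysis window by MMF use. SAP 5.2 removes participants who took no study medication. Read literally, these could leave the control arm without data for the comparison. On the other hand, Table 1 schedules adverse-event recording from the run-in onwards without distinguishing arms, so the documents point both ways.

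The change should be made. It concerns how harms are interpreted and reported; it does not touch the primary efficacy inference or the sample size.

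**What to change.** - **SAP 4.4:** delete *and safety* from the sentence that sets the 0.05 rule.
- **SAP 6.4:** keep the opening sentence. Replace the Fisher sentence with wording such as: *for each adverse-event category, the number and percentage of patients in each arm and the risk difference with its 95% confidence interval (Newcombe or Miettinen-Nurminen) will be reported; absence of harm will not be inferred from p≥0.05.*
- **Fisher p-values:** either drop them or keep them explicitly labelled nominal and descriptive. Both options remove the contradiction.
- **Recording and safety set:** reconcile Protocol section 9 (Collection), SAP 3.7.1 and SAP 5.2 with each other and with Table 1, so that control-arm risks exist for this comparison.

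The cost of the analysis change is SAP wording and one extra column in the adverse-event tables. The downside is that the safety tables lose a formal significance verdict.
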